### Feasibility and Acceptability

Feasibility will be monitored by tracking the completion of surgical procedures, follow-up adherence, and compliance with distraction protocols. Acceptability will be inferred based on the absence of withdrawals and participants’ tolerance to the intervention schedule. As of June 2025, no participant dropouts or major protocol deviations have been recorded.

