### Primary Objective

The primary objective will be to compare the outcomes of unilateral Le Fort I advancement and dentoalveolar transport distraction in the closure of alveolar gap, arch form, segment stability, and soft tissue healing.

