### Sample Size Calculation

The minimum required sample size was calculated using the standard formula for comparing 2 independent means, as shown below:

$$N=\frac{{\left(Z_{\alpha }+Z_{\beta }\right)}^{2}\left(P_{1}\left(1-P_{1}\right)+P_{2}\left(1-P_{2}\right)\;\right)}{{\left(P2-P1\right)}^{2}}$$

$$Z_{\alpha }=1.64$$

α= Type I error at 5%

$$Z_{\beta }=0.84$$

β= Type II error at 20%

The following parameters were used for the sample size calculation:

Improved facial esthetic and balance in maxillary DO=94%Improved facial esthetic and balance in maxillary unilateral Le Fort 1 osteotomy=44% (estimated clinically significant difference=50%)Difference (P2−P1)=50%Minimum sample size N=2×(1.64+0.84)^2^ (0.94) (1‐0.94) + 0.44(1‐0.44)/(0.50)^2^=7 each in 2 groupsSample size=14, with 7 in each group

Using a 2-sided z test with *α*=.05 and power of 80%, assuming a success rate of 94% in the dentoalveolar transport distraction group and 44% in the unilateral Le Fort I advancement group, the required sample size is 7 per group (N=14). This includes a 50% absolute effect size and accounts for variability in response.

The 50% effect size estimate was based on the internal pilot data and clinical observations. However, we acknowledge the possibility of overestimation. A sensitivity analysis will also consider a 40% effect size, which would require a larger sample and will be addressed in future studies.

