### The Unilateral Le Fort I Advancement Group

Orthodontic preparation will be done similarly. A horizontal incision will be made, and a mucoperiosteal flap will be raised to expose the anatomical landmarks. Standard Le Fort I and palatal osteotomies will be carried out. The segment will be medially repositioned and fixed using a surgical splint and bone plates. The flap will be closed with 3‐0 Vicryl sutures.

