## Results

As of June 2025, patient recruitment, which began in April 2023, is ongoing. Out of 14 intended participants, 12 (85%) have been enrolled (with 7 in the dentoalveolar transport distraction group and 5 in the unilateral Le Fort I advancement group). The enrolled cohort includes 8 male individuals and 4 female individuals, with a mean age of 16.8 (SD 3.9; range 10-23) years. The average cleft width among the participants was 1.5 (SD 0.34; range 1.0-2.1) cm.

Data collection is anticipated to conclude by December 2025, and the results are expected to be published in 2026.

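### Zero withdrawals in 7 or 14 patients cannot support the planned inference of acceptability; the count should be reported with an exact interval instead (minor)

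*Protocol article*

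**What the plan says.** The Feasibility and Acceptability section of the protocol article has three sentences. The first is on feasibility: "Feasibility will be monitored by tracking the completion of surgical procedures, follow-up adherence, and compliance with distraction protocols". The second sets the basis for judging acceptability: "Acceptability will be inferred based on the absence of withdrawals and participants’ tolerance to the intervention schedule". The third gives the position so far: "As of June 2025, no participant dropouts or major protocol deviations have been recorded".

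No tolerable withdrawal rate, margin or confidence bound accompanies the second sentence. It does not say whether acceptability is judged for each technique or for all participants together.

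The Sample Size Calculation section plans 7 patients per group, 14 in all. The Results section reports 12 enrolled, "with 7 in the dentoalveolar transport distraction group and 5 in the unilateral Le Fort I advancement group".

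Acceptability appears in neither objective. The primary objective compares the techniques "in the closure of alveolar gap, arch form, segment stability, and soft tissue healing". It is not among the primary or secondary outcomes, and the Statistical Analysis section promises 95% confidence intervals for outcome measures only.

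**The concern.** The sentence treats the absence of an event as grounds for a positive conclusion. With so few patients, no withdrawals is a likely result even if a technique has an appreciable withdrawal rate. An investigator who followed the text could write that the techniques were acceptable when the data would not exclude a withdrawal rate of a quarter (all patients) or two fifths (one group).

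The count also does not mean quite the same thing in the two groups. In group A the operation is followed by latency, daily distraction and consolidation, and a patient can stop during distraction. In group B the movement is completed at surgery: "The segment will be medially repositioned and fixed using a surgical splint and bone plates". After the operation, what a group B patient can abandon is mainly follow-up. A single withdrawal count mixes these two kinds of event.

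What is at stake is a secondary claim about acceptability, not the comparison of gap closure, arch form, stability or healing.

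**Working it through.** **Inputs from the article**
- Planned size: 7 per group, 14 in total (Sample Size Calculation).
- Enrolled by June 2025: 7 and 5, 12 in total (Results).
- Dropouts by June 2025: none (Feasibility and Acceptability). I take dropouts to mean withdrawals.

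**Input that is assumed**
- True withdrawal rate q. The article gives none, so 5%, 10% and 20% are shown.

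**The plan's own figure.** The article states no error rate or bound for acceptability, so there is none to reproduce. The group size can be checked from its formula, which uses "assuming a success rate of 94% in the dentoalveolar transport distraction group and 44% in the unilateral Le Fort I advancement group":

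(1.64 + 0.84)² × (0.94 × 0.06 + 0.44 × 0.56) / 0.50² = 6.1504 × 0.3028 / 0.25 = 7.45, reported as 7.

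That size was chosen for a comparison of success rates and was not set with withdrawals in view.

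**Step 1: what a zero count excludes.** After 0 events in n patients, the exact (Clopper-Pearson) two-sided 95% upper limit is 1 − 0.025^(1/n), and the one-sided 95% limit is 1 − 0.05^(1/n). Neither needs an assumed rate.

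| Zero withdrawals in | Two-sided limit | One-sided limit |
|---|---|---|
| 5 (group B, June 2025) | 52.2% | 45.1% |
| 7 (one full group) | 41.0% | 34.8% |
| 12 (all enrolled, June 2025) | 26.5% | 22.1% |
| 14 (full sample) | 23.2% | 19.3% |

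To bring the one-sided limit below 10% with no events, n must exceed ln 0.05 / ln 0.9 = 28.4, so 29 patients.

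**Step 2: how easily the withdrawal part is met.** With independent patients, P(no withdrawals) = (1 − q)^n.

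| n | q = 5% | q = 10% | q = 20% |
|---|---|---|---|
| 5 | 77.4% | 59.0% | 32.8% |
| 7 | 69.8% | 47.8% | 21.0% |
| 14 | 48.8% | 22.9% | 4.4% |

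**Step 3: the second part of the criterion.** The sentence also requires tolerance of the schedule, so the figures in Step 2 are ceilings for the full criterion. As an illustration only, suppose q = 10% and each of 7 patients independently tolerates the schedule with probability 90%. Both parts are then met with probability (0.9 × 0.9)^7 = 22.9%. At 80% tolerance it is (0.9 × 0.8)^7 = 10.0%.

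If tolerance were itself judged by no patient failing to tolerate the schedule, the limits in Step 1 would apply to intolerance as well: 0 of 7 would leave up to 41%.

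**The case against.** **The criterion has two parts.** Tolerance is named beside withdrawals, so it would be wrong to say that a technique which one patient in ten abandons is declared acceptable about half the time. This stands. The 48% covers only the withdrawal part, in a group of 7, at an assumed rate of 10%.

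**The unit is not stated.** The section refers to participants generally, and over 14 patients the same probability is 23%. This also stands, so neither reading should be presented as the plan's. The conclusion survives either way, because even 0 of 14 leaves an upper limit of 23%.

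**There is no formal declaration.** The paragraph is about monitoring and attaches no pass or fail consequence. A reader might infer that the study will pronounce both techniques acceptable, or that it offers the absence of dropouts as support. The article says neither, and its third sentence is a dated status report. What remains is that the second sentence does commit to inferring acceptability.

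**Withdrawal is possible in both groups.** A reader might infer that zero withdrawals in group B is nearly automatic. The article does not support this. Both groups have orthodontic preparation before surgery and follow-up to 1 year, and either can be abandoned. Only the narrower point holds: group A alone has a distraction phase after surgery that can be stopped.

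**Details may lie elsewhere.** A condensed article may leave the definition of tolerance and the reporting of descriptive counts to a fuller document. That is fair, and the point does not rest on the missing definition. It rests on the inference that the sentence states. The feasibility sentence already tracks distraction compliance and follow-up adherence, so part of the data needed for the fix is planned.

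**Conclusion.** The point holds in a limited form. Absence of withdrawals in this sample cannot by itself support acceptability: the exact two-sided 95% upper limit is 41% for a full group of 7, 52% for the group B of 5 enrolled in June 2025, 26% for the 12 enrolled, and 23% for all 14. These limits assume only independent patients with a common withdrawal rate. The probabilities of 48% (n = 7) and 23% (n = 14) also rest on the assumed 10% rate, and they are upper bounds on meeting the two-part criterion. Tolerance, as the article describes it, has no stated measure that would make good the weakness. The count is only partly comparable between the groups.

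Severity is minor. Acceptability is not an objective or an outcome, and no main comparison depends on it.

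**What to change.** Replace the whole sentence "Acceptability will be inferred based on the absence of withdrawals and participants’ tolerance to the intervention schedule" with a statement to this effect:
- Withdrawals will be reported per group and overall as counts with exact (Clopper-Pearson) 95% confidence intervals.
- Discontinuation of distraction in group A will be shown separately from loss to follow-up in both groups.
- Tolerance of the schedule will be described only.
- Zero withdrawals in a sample of this size will not by itself be taken as evidence of acceptability.

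The cost is a change of wording and a few exact intervals, with no more patients to recruit. The article already plans to track distraction compliance and follow-up adherence. The downside is a less favourable statement about acceptability: even with no withdrawals, the report would have to show 0 of 7 with an interval reaching 41%.

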### Primary Objective

The primary objective will be to compare the outcomes of unilateral Le Fort I advancement and dentoalveolar transport distraction in the closure of alveolar gap, arch form, segment stability, and soft tissue healing.

### Secondary Objectives

The secondary objectives will be to assess the intragroup outcomes over time for each technique and to evaluate patient-specific variables (eg, age and cleft width) that may influence outcome variation.

### Sample Size Calculation

The minimum required sample size was calculated using the standard formula for comparing 2 independent means, as shown below:

$$N=\frac{{\left(Z_{\alpha }+Z_{\beta }\right)}^{2}\left(P_{1}\left(1-P_{1}\right)+P_{2}\left(1-P_{2}\right)\;\right)}{{\left(P2-P1\right)}^{2}}$$

$$Z_{\alpha }=1.64$$

α= Type I error at 5%

$$Z_{\beta }=0.84$$

β= Type II error at 20%

The following parameters were used for the sample size calculation:

Improved facial esthetic and balance in maxillary DO=94%Improved facial esthetic and balance in maxillary unilateral Le Fort 1 osteotomy=44% (estimated clinically significant difference=50%)Difference (P2−P1)=50%Minimum sample size N=2×(1.64+0.84)^2^ (0.94) (1‐0.94) + 0.44(1‐0.44)/(0.50)^2^=7 each in 2 groupsSample size=14, with 7 in each group

Using a 2-sided z test with *α*=.05 and power of 80%, assuming a success rate of 94% in the dentoalveolar transport distraction group and 44% in the unilateral Le Fort I advancement group, the required sample size is 7 per group (N=14). This includes a 50% absolute effect size and accounts for variability in response.

The 50% effect size estimate was based on the internal pilot data and clinical observations. However, we acknowledge the possibility of overestimation. A sensitivity analysis will also consider a 40% effect size, which would require a larger sample and will be addressed in future studies.

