### Primary Outcome

The primary outcomes evaluated in this study will be as follows:

Closure of the alveolar gap: measured clinically and radiographically (ie, CBCT) at 5 time points: preoperatively; immediately after surgery; and at 1, 3, and 6 months and 1 year of follow-upArch form: classified (U-shaped, V-shaped, or asymmetrical) via models and radiographs at each follow-up

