## Discussion

### Anticipated Findings

This prospective observational study compares 2 graftless surgical techniques—unilateral Le Fort I advancement and dentoalveolar transport distraction—for the management of large alveolar clefts. On the basis of prior evidence, we anticipate that dentoalveolar transport distraction may achieve more predictable closure of wide alveolar gaps due to its capability for simultaneous bone and soft tissue regeneration through gradual mechanical tension [8,9]. Unilateral Le Fort I advancement, while traditionally used for midfacial hypoplasia and skeletal advancement, may offer improved esthetic facial projection but may be limited by the extent of cleft closure, particularly in large defects [10]. This study will evaluate and compare the clinical, radiographic, and soft tissue healing outcomes of both interventions to identify their respective advantages.

Several studies have demonstrated the effectiveness of dentoalveolar transport distraction in achieving successful cleft closure, even in patients for whom conventional bone grafting had failed [8,9,12]. These techniques exploit the principle of DO, first introduced to the craniofacial skeleton by McCarthy et al [7] and later adapted to the alveolar ridge [8]. Similarly, Le Fort I osteotomy, first described for cleft-related maxillary retrusion, has shown good results in terms of facial profile improvement and occlusion correction [11]. However, few prospective studies have evaluated these 2 methods head-to-head in a controlled population with similar cleft widths, making direct clinical comparison difficult. This study aims to address this gap by applying standardized clinical and radiographic outcome measures across both groups.

The study’s strengths include its prospective design, structured follow-up, and the use of objective evaluation tools, including CBCT for gap measurements and standardized scales such as the Landry wound healing scale and the bone stability scale. By focusing on large clefts (≥1 cm) and excluding patients with bilateral defects or prior interventions, the study enhances internal validity. Limitations include the relatively small sample size, which may limit generalizability, and the nonrandom allocation of patients to treatment groups based on clinical feasibility. However, multivariate regression will be used to adjust for baseline differences, and standardized surgical and postoperative protocols will minimize procedural variability.

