Although not formally implemented in this study, future work could explore integrating adaptive patient-reported outcome measures such as the Cleft Lip and Palate Patient-Reported Outcome Measure platform to assess quality of life and surgical satisfaction [13].

Depending on the outcomes, this study may inform clinical treatment pathways for managing wide alveolar clefts using graftless techniques. Future research could expand to include long-term assessment of relapse, dental eruption across the regenerated cleft, and patient-reported outcome measures such as quality of life and esthetic satisfaction. Integration with 3D simulation and planning tools could further improve precision in surgical execution.

Recent reviews and bibliometric analyses show a marked increase in research on maxillary distraction protocols, reflecting growing global interest in optimizing cleft management [14].

Findings from this study will be submitted for publication in peer-reviewed journals and presented at national and international maxillofacial surgery conferences. Additionally, results will be shared with our institution’s multidisciplinary cleft care teams to inform clinical decision-making. If substantial differences are observed, the study may contribute to the development of evidence-based treatment guidelines for wide alveolar clefts.

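### The 80% power and N=14 are calculated for improved facial esthetics, which is not a listed outcome, so the stated power applies to none of the outcomes the study will analyze

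*Protocol article*

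**What the plan says.** The Sample Size Calculation section works from two proportions: "Improved facial esthetic and balance in maxillary DO=94" percent for distraction, and "Improved facial esthetic and balance in maxillary unilateral Le Fort 1 osteotomy=44" percent for the comparator. The 50-point gap between them is called clinically significant, and its source is given: "The 50% effect size estimate was based on the internal pilot data and clinical observations". A summary paragraph in the same section then claims 80% power with 7 per group, "assuming a success rate of 94% in the dentoalveolar transport distraction group and 44% in the unilateral Le Fort I advancement group". Success is not defined there. The paragraph adds: "This includes a 50% absolute effect size and accounts for variability in response".

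The Primary Outcome section names two outcomes. The first is "Closure of the alveolar gap: measured clinically and radiographically", followed over time; the second is arch form in three categories. The Secondary Outcomes section names segment stability on a 5-point scale and soft tissue healing on the Landry scale. The same four appear in the Introduction's hypotheses, in Outcome Measures and Data Collection, and in the Primary Objective. The Statistical Analysis section names tests for these four only.

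Esthetics appears in three other places:

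- The Introduction lists it among the kinds of outcome to be compared.
- The Discussion (Anticipated Findings) says that Le Fort I "may offer improved esthetic facial projection but may be limited by the extent of cleft closure".
- The Discussion places "patient-reported outcome measures such as quality of life and esthetic satisfaction" in future research.

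**The concern.** A power statement holds for one endpoint, one test and one assumed effect. Here the endpoint is a binary rating of facial esthetics and balance, and the study lists no such measure. Calling the same percentages a success rate hides this. The procedure label also moves from maxillary DO to dentoalveolar transport distraction, which the Introduction describes as a subset of DO. A reader would naturally take success to mean cleft closure.

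The 80% figure is the article's only justification for 14 patients. If it stands, a non-significant result on gap closure or arch form could be read as coming from an adequately powered comparison. The Discussion says that the study may contribute to treatment guidelines, so that misreading would have consequences.

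**Working it through.** **1. Reproduce the plan's figure.** Inputs from Sample Size Calculation: P1 = 0.94, P2 = 0.44, Zα = 1.64, Zβ = 0.84.

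- Variance term: 0.94 × 0.06 + 0.44 × 0.56 = 0.0564 + 0.2464 = 0.3028.
- n per group = (1.64 + 0.84)² × 0.3028 / 0.50² = 6.1504 × 0.3028 / 0.25 = 7.45.

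The stated 7 is this value rounded down. The figure is therefore a calculation for facial esthetics and nothing else. (Separately, 1.64 is a one-sided value although the section states a two-sided test. This point does not depend on that.)

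**2. Look for a listed outcome to which 94% and 44% could belong.**

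| Candidate | Where | Linked to 94%/44%? |
|---|---|---|
| Gap closure, CBCT and clinical | Primary Outcome | No rate, SD or target difference given |
| Arch form, three categories | Primary Outcome | No category probabilities given |
| Segment stability, 1 to 5 | Secondary Outcomes | No distribution given |
| Landry healing, 1 to 5 | Secondary Outcomes | No distribution given |
| Successful closure, binary, in a logistic model | Postoperative Care | Undefined, no assumed rate |
| Esthetic outcomes | Introduction | Aim only; no instrument, endpoint or analysis |
| Lateral cephalograms | Preoperative Assessment | Preoperative, to assess the cleft; not an outcome |

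None carries the sample size inputs, and no replacement N can be derived for any of them from the article.

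**3. What 14 patients give for a continuous gap measure, in SD units.** Two-sample t test, two-sided α = 0.05. Group sizes are 7+7 as planned, and 7+5 as enrolled by June 2025 (Results section).

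- The difference d with 80% power comes from the noncentral t distribution with noncentrality d × √(n₁n₂/(n₁+n₂)). For 7+7 (12 df), d = 1.63. For 7+5 (10 df), d = 1.82.
- Power at 7+7 for true differences of 0.5, 0.8, 1.0 and 1.2 SD is 14%, 28%, 41% and 54%.
- Expected 95% CI half-width at 7+7: 2.179 × √(1/7 + 1/7) = 2.179 × 0.5345 = 1.16 SD.
- Expected 95% CI half-width at 7+5: 2.228 × √(1/7 + 1/5) = 2.228 × 0.5855 = 1.30 SD.

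**4. Millimetres, as a range only.** The one SD in the article is for baseline cleft width, 0.34 cm (Results). The SD of the gap after treatment is not given. Assuming half, one and one and a half times 3.4 mm:

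| Assumed SD | Detectable, 7+7 (1.632 × SD) | Detectable, 7+5 (1.821 × SD) | CI half-width, 7+7 (1.165 × SD) | CI half-width, 7+5 (1.305 × SD) |
|---|---|---|---|---|
| 1.7 mm | 2.8 mm | 3.1 mm | 2.0 mm | 2.2 mm |
| 3.4 mm | 5.5 mm | 6.2 mm | 4.0 mm | 4.4 mm |
| 5.1 mm | 8.3 mm | 9.3 mm | 5.9 mm | 6.7 mm |

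The mean cleft width is 15 mm. These rows only illustrate how strongly the answer depends on the SD.

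**The case against.** Several things can be said for the protocol.

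- **Esthetics is an aim.** The Introduction says so, and a journal article condenses the full protocol, so an esthetic rating might exist elsewhere. A reader might infer that esthetics is wholly outside the study; the article does not support that. What stands is narrower: where the article lists outcomes, hypotheses and analyses, none is esthetic. The future-research remark does not settle it either, since it concerns patient-reported measures and not clinician ratings.
- **A binary closure outcome is mentioned.** This is true, and gap closure is not analyzed only as a continuous variable. But success is undefined, and 94% and 44% were introduced as esthetic rates.
- **The Discussion may contradict the calculation.** A reader might infer that the authors expect Le Fort I to be esthetically better while sizing the study on its being 50 points worse. The sentence is hedged, concerns facial projection only, and may mean improvement over the preoperative state. There is tension that deserves a clarifying line, but no firm contradiction.
- **A detectable difference of 5.5 mm might be taken as established.** It is not. In group A, distraction continues until the gap closes, so residual gaps may cluster near zero with an SD unlike 3.4 mm. The plan also allows a Mann-Whitney test and adjustment for baseline width.
- **The limits are partly admitted.** The article concedes that the effect may be overestimated and that the sample is small. Both remarks concern size; neither discloses that the effect belongs to another endpoint.

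**Conclusion.** The point holds. N=14, 80% power and the 50-point difference were derived for improved facial esthetics and balance, and they apply to none of the four listed outcomes. Relabelling the inputs as a success rate does not change that.

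For a continuous gap measure, the study has 80% power only for differences of about 1.63 SD (7+7) or 1.82 SD (7+5), with 95% CI half-widths of about 1.16 and 1.30 SD. These values assume roughly normal data with equal variances and an unadjusted two-sided 5% t test; they need no assumption about the SD itself.

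A reader might go further and infer that the study is underpowered for its true effect on closure. The article gives no target difference or SD for closure, so that cannot be shown. What can be said is that no power is established for any listed outcome.

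**What to change.** In the Sample Size Calculation section:

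1. Withdraw the statement that 14 patients give 80% power, as far as it concerns this study's outcomes.
2. State that 94% and 44% are rates of improved facial esthetics and balance, and drop the success-rate label.
3. Report the precision that 14 patients give for both stated primary outcomes. For gap closure treated as continuous, give the standardized values above. Give millimetres only over a range of assumed SDs. For arch form, give CI widths for differences in category proportions under stated assumptions.
4. Describe N=14 as a feasibility number only if the investigators confirm that it was; the article currently presents it as calculated.

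As a minor point, add a sentence on how the esthetic assumption in the calculation fits the Discussion's remark on facial projection after Le Fort I.

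The cost is rewording and the loss of an unsupported power claim. Enrollment (12 of 14 by June 2025), procedures and assessments are unaffected.

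### The sample size is declared two-sided with 80% power but uses the one-sided z of 1.64 and rounds 7.45 down to 7; 7 per group gives about 67% power at best

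*Protocol article*

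**What the plan says.** All of the calculation is in the protocol article, Methods, Sample Size Calculation.

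- The formula is introduced as "calculated using the standard formula for comparing 2 independent means". The expression printed below it is the unpooled formula for two proportions, with no leading factor of 2.
- The error rate is given as "α= Type I error at 5" percent, with Z_alpha = 1.64 and Z_beta = 0.84.
- The worked line begins "Minimum sample size N=2×(1.64+0.84)^2^ (0.94") and is set equal to 7 in each of two groups.
- The summary paragraph reads "Using a 2-sided z test with *α*=.05 and power of 80" percent, "assuming a success rate of 94% in the dentoalveolar transport distraction group" and "44% in the unilateral Le Fort I advancement group". From this it concludes that "the required sample size is 7 per group (N=14").

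The Results section reports the enrolment as of June 2025: "with 7 in the dentoalveolar transport distraction group and 5 in the unilateral Le Fort I advancement group". The Statistical Analysis section assigns categorical outcomes to a chi-square or Fisher exact test, whichever is appropriate.

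**The concern.** Z_alpha = 1.64 and a two-sided 5% test cannot both describe one calculation. The result of the displayed formula is also rounded down, although the section calls it a minimum. The factor of 2 in the worked line agrees neither with the displayed formula nor with a result of 7 per group.

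What is at stake is how the results will be read. The null hypothesis in the Introduction is worded as the absence of a detectable difference, and the abstract and Discussion expect the findings to guide the choice of operation and possibly to inform guidelines. A reader told that power was 80% will give a non-significant result more weight as evidence of similarity than 14 patients can support.

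**Working it through.** **Inputs (all from Sample Size Calculation).** p1 = 0.94, p2 = 0.44, difference 0.50, Z_alpha = 1.64, Z_beta = 0.84, 7 per group, declared test two-sided at 0.05.

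**1. Reproducing the plan's figure.** Displayed formula: n per group = (Z_alpha + Z_beta)² × [p1(1−p1) + p2(1−p2)] / (p2−p1)².

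- (1.64 + 0.84)² = 6.1504
- 0.94 × 0.06 + 0.44 × 0.56 = 0.0564 + 0.2464 = 0.3028
- 6.1504 × 0.3028 / 0.25 = **7.45 per group**

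The stated 7 is this value rounded down. A minimum requirement rounds up to 8.

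**2. The worked line.** With the displayed formula's brackets restored, its factor of 2 gives 2 × 7.45 = **14.90**. That is not 7 per group. Read as a total for both groups, it rounds up to 15, or 16 with equal groups, not 14.

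**3. The declared two-sided test.** Replacing 1.64 by 1.96: (1.96 + 0.84)² = 7.84, and 7.84 × 0.3028 / 0.25 = 9.50, so **10 per group**. Other standard two-sided versions need more:

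| Method, two-sided 0.05, 80% power | Per group |
|---|---|
| Unpooled (the plan's formula) | 10 |
| Arcsine | 11 |
| Pooled variance | 13 |
| Exact Fisher (first n to reach 80%) | 15 |
| Pooled with continuity correction | 16 |

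None gives 7.

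**4. Power at 7 + 7.** By the plan's approximation, 0.50 / √(0.3028/7) = 2.404.

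- Two-sided: Φ(2.404 − 1.96) = Φ(0.444) = **67%**
- One-sided: Φ(2.404 − 1.645) = Φ(0.759) = **77.6%**

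Other two-sided approximations give 61% (arcsine) and 53% (pooled variance). Summing binomial probabilities over all possible outcomes, with rejection at two-sided 0.05, gives **51%** for the pooled z test and **25%** for Fisher's exact test.

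The Fisher figure is low because the test is coarse at this size. An observed 7/7 versus 3/7, close to the planned 94% versus 44%, has a one-tail probability of C(7,3)/C(14,10) = 35/1001 = 0.035. The opposite extreme is equally likely, so two-sided p = 0.070, not significant.

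**5. The enrolled 7 + 5.** 0.50 / √(0.0564/7 + 0.2464/5) = 0.50 / 0.2394 = 2.088, and Φ(2.088 − 1.96) = **55%**. Exact Fisher power is **42%**. This exceeds the 25% at 7 + 7 only because the attainable p-values differ between the two layouts; it is no argument for fewer patients.

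**6. The 40-point difference that the section mentions.** The plan gives no rates for it, so these are assumptions, each keeping one of the stated rates.

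- 94% versus 54%: 0.40 / √(0.3048/7) = 1.917, and Φ(1.917 − 1.96) = **48%**
- 84% versus 44%: 0.40 / √(0.3808/7) = 1.715, and Φ(1.715 − 1.96) = **40%**

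**The case against.** The strongest reply accepts the arithmetic and disputes its weight.

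- **The factor of 2 costs no power.** This is right. It did not produce the 7 and can be read as a conversion to a two-group total. It is a notation error. Rounding down is also a small part of the loss: on the one-sided reading, 77.6% against 80%. Most of the shortfall comes from using 1.64 instead of 1.96.
- **The Fisher figure is a low point.** This is also fair. Fisher power is 25% at 7 + 7 but 38% at 8 + 8, and the section names a z test. The Fisher figure should be read as the lower end of a range, with 67% by the plan's own formula at the upper end. It remains relevant because the Statistical Analysis section names Fisher's test as an option and expected counts will be small.
- **The rates concern facial esthetics and balance, which is not among the listed outcomes.** True. A corrected power figure therefore still says nothing about gap width or three-category arch form. That is a further limit of the calculation and does not rescue the 80% claim.
- **The plan already shows caution.** It promises 95% confidence intervals, concedes that the effect may be overestimated, and lists the small sample as a limitation. But that limitation is tied to generalizability, and nothing withdraws the statement that 7 per group gives 80% power. The plan also nowhere says that a non-significant result will be read as no difference, so that harm is a risk and not a stated intention.

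**Conclusion.** The concern holds. For the test as declared, 7 per group does not give 80% power under any version checked: 67% by the plan's own approximation, 51% by exact pooled z and 25% by exact Fisher. The chance of missing even a true 50-point difference is therefore about 33% to 75%, against the stated 20%. Reading the test as one-sided does not save the claim, since 77.6% is still short and the text says two-sided. The plan's own formula requires 10 per group.

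These figures take the plan's rates of 94% and 44% at face value and treat the outcome as binary, as the calculation does. The size of the shortfall depends on the variance form and the test; its existence does not.

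**What to change.** Rewrite the Sample Size Calculation section:

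1. Call the formula one for two independent proportions.
2. Use 1.96 with the declared two-sided test, remove the factor of 2, restore the brackets in the worked line and round up. The result is 10 per group.
3. Remove the statement that 7 per group gives 80% power. Give instead the power at 7 + 7 for 94% versus 44%: about 67% by the formula and about 25% with Fisher's exact test, naming the test each time and saying that the figure applies to the binary esthetic endpoint used in the calculation.
4. State the real basis for 14 patients. If it is feasibility, say so.
5. Keep the planned 95% confidence intervals as the main basis for interpretation, and add that a non-significant result will not be taken as evidence of no difference.

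No extra patients, visits or measurements are needed. With 12 of 14 enrolled and data collection due to end in December 2025, the cost is one rewritten section and a less favourable power statement.
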